## Abstract

**Background::**

Patients on dialysis are commonly prescribed multiple medications (polypharmacy), many of which are potentially inappropriate medications (PIMs). Potentially inappropriate medications are associated with an increased risk of falls, fractures, and hospitalization. MedSafer is an electronic tool that generates individualized, prioritized reports with deprescribing opportunities by cross-referencing patient health data and medications with guidelines for deprescribing.

**Objectives::**

Our primary aim was to increase deprescribing, as compared with usual care (medication reconciliation or MedRec), for outpatients receiving maintenance hemodialysis, through the provision of MedSafer deprescribing opportunity reports to the treating team and patient empowerment deprescribing brochures provided directly to the patients themselves.

**Design::**

This controlled, prospective, quality improvement study with a contemporary control builds on existing policy at the outpatient hemodialysis centers where biannual MedRecs are performed by the treating nephrologist and nursing team.

**Setting::**

The study takes place on 2 of the 3 outpatient hemodialysis units of the McGill University Health Centre in Montreal, Quebec, Canada. The intervention unit is the Lachine Hospital, and the control unit is the Montreal General Hospital.

**Patients::**

A closed cohort of outpatient hemodialysis patients visit one of the hemodialysis centers multiple times per week for their hemodialysis treatment. The initial cohort of the intervention unit includes 85 patients, whereas the control unit has 153 patients. Patients who are transplanted, hospitalized during their scheduled MedRec, or die before or during the MedRec will be excluded from the study.

**Measurements::**

We will compare rates of deprescribing between the control and intervention units following a single MedRec. On the intervention unit, MedRecs will be paired with MedSafer reports (the intervention), and on the control unit, MedRecs will take place without MedSafer reports (usual care). On the intervention unit, patients will also receive deprescribing patient empowerment brochures for select medication classes (gabapentinoids, proton-pump inhibitors, sedative hypnotics and opioids for chronic non-cancer pain). Physicians on the intervention unit will be interviewed post-MedRec to determine implementation barriers and facilitators.

**Methods::**

The primary outcome will be the proportion of patients with 1 or more PIMs deprescribed on the intervention unit, as compared with the control unit, following a biannual MedRec. This study will build on existing policies aimed at optimizing medication therapy in patients undergoing maintenance hemodialysis. The electronic deprescribing decision support tool, MedSafer, will be tested in a dialysis setting, where nephrologists are regularly in contact with patients. MedRecs are an interdisciplinary clinical activity performed biannually on the hemodialysis units (in the Spring and Fall), and within 1 week following discharge from any hospitalization. This study will take place in the Fall of 2022. Semi-structured interviews will be conducted among physicians on the intervention unit to determine barriers and facilitators to implementation of the MedSafer-supplemented MedRec process and analyzed according to grounded theory in qualitative research.

**Limitations::**

Deprescribing can be limited due to nephrologists’ time constraints, cognitive impairment of the hemodialyzed patient stemming from their illness and complex medication regimens, and lack of sufficient patient resources to learn about the medications they are taking and their potential harms.

**Conclusions::**

Electronic decision support can facilitate deprescribing for the clinical team by providing a nudge reminder, decreasing the time it takes to review and effectuate guideline recommendations, and by lowering the barrier of when and how to taper. Guidelines for deprescribing in the dialysis population have recently been published and incorporated into the MedSafer software. To our knowledge, this will be the first study to examine the efficacy of pairing these guidelines with MedRecs by leveraging electronic decision support in the outpatient dialysis population.

**Trial registration::**

This study was registered on Clinicaltrials.gov (NCT05585268) on October 2, 2022, prior to the enrolment of the first participant on October 3, 2022. The registration number is pending at the time of protocol submission.

## Introduction

### Background and Rationale

Patients with end-stage kidney disease (ESKD) who require dialysis are prescribed an average of 10 to 12 daily medications, often by 4 to 5 different clinicians, amounting to as many as 19 pills per day.^1-4^ The dialysis patient population has one of the heaviest pill burdens of all chronic conditions due to concurrent treatment of co-existing conditions such as hypertension, vascular disease, and diabetes,^
4
^ as well as treatment of complications of ESKD itself (eg, increased propensity for bleeding, bone mineral metabolism disorders, pruritus, pain, and insomnia).

More than 90% of dialysis patients take 5 or more medications (polypharmacy),^2,5^ contributing to medication overload.^6,7^ Furthermore, more than 90% are prescribed 1 or more potentially inappropriate medications (PIMs)^1,4,8^; PIMs are associated with an increased risk of harm (often through adverse drug events, ADEs) or they have a relatively low chance for benefit and merely contribute to a patient’s pill burden.^2,4,7^ Adverse drug events such as falls, fractures, and cognitive impairment can occur as a direct result of PIMs, or due to drug-drug interactions, both of which are more common with polypharmacy.^9,10^ Polypharmacy and ADEs contribute to emergency room visits, hospital admissions, loss of autonomy, and premature death.^11-13^ There is, therefore, a pressing need for pragmatic, scalable interventions to address polypharmacy in dialysis patients.^3,14,15^

We previously demonstrated that MedSafer, an electronic decision support tool, can increase deprescribing for hospitalized older adults and for people residing in long-term care homes.^16,17^ MedSafer identifies deprescribing opportunities by electronically cross-referencing a person’s usual medication list and medical comorbidities, with a curated ruleset containing evidence-based deprescribing guidelines (based on criteria from the American Geriatrics Society,^
18
^ STOPP,^
19
^ and Choosing Wisely^
20
^).^
17
^ MedSafer stratifies deprescribing opportunities into high-risk, intermediate-risk, or little added value categories. High risk implies there is an elevated risk of developing ADEs; intermediate risk implies that the harms must be weighed against the benefits of the drug; and drugs of little added value simply increase the pill burden of a patient or have evidence demonstrating no effect. Examples of a typical deprescribing report and of different drugs that fall into the 3 categories can be found in the Supplement of the MedSafer Study.^
16
^ Our large cluster randomized clinical trial of older adults hospitalized in the acute care setting (N = 5698) included 140 patients receiving maintenance hemodialysis. The net deprescribing rate among dialysis patients was 9.4% (95% confidence interval [CI] = 1.3%-17.6%) higher in the intervention period compared with the control period. While effective, the general population in the study benefited from a much higher rate of deprescribing (absolute increase of 22.2%, 95% CI = 16.9%-27.4%).^
16
^ At that time, no dialysis-specific rules were integrated into the MedSafer software, and patients were enrolled during a time of acute illness.

Since then, McIntyre et al^
15
^ have developed deprescribing algorithms specifically for hemodialysis patients in a quality improvement study.^4,8^ However, like most guidelines, there are barriers to implementation and uptake. Guidelines for deprescribing contain long lists of rules that preclude memorization; some may contain conflicting recommendations for patients taking 10 to 15 medications; and not all guidelines explain how to deprescribe (eg, when and how to taper and what rebound symptoms to watch out for).^
2
^,^21-23^ We therefore integrated the dialysis-specific deprescribing recommendations into the MedSafer ruleset, coupled them with links to patient deprescribing empowerment brochures, and added instructions for tapering where required.

### Objectives

Our primary aim in this study is to increase deprescribing, as compared with usual care (medication reconciliation or MedRec), for outpatients receiving maintenance hemodialysis, through the provision of MedSafer deprescribing opportunity reports to the treating team and patient empowerment deprescribing brochures provided directly to the patients.

### Study Design

This is a controlled, prospective, quality improvement study, with a contemporary control. Publication of the study will follow the SQUIRE 2.0 reporting guideline: Revised Standard for Quality Improvement Reporting Standards.^
24
^ Relevant elements of SQUIRE 2.0 have been addressed in this protocol (Supplemental Appendix). This protocol follows the SPIRIT^
25
^ checklist (Standard Protocol Items: Recommendations for Interventional Trials) and is ordered according to the *Trials* Journal Structured Study Protocol Template.^
26
^

## Methods: Participants, Intervention, and Outcomes

### Study Setting

The study takes place on the 2 largest (of 3) outpatient hemodialysis units at the McGill University Health Centre in Montreal, Quebec, Canada. The intervention unit is the Lachine Hospital dialysis unit, and the control unit is the Montreal General Hospital dialysis unit. This assignment was random.

### Eligibility Criteria

#### Inclusion criteria

Outpatients receiving maintenance hemodialysis on one of the two participating units.Aged 18 years and over.One or more PIMs identified.

#### Exclusion criteria

Patient is currently hospitalized or is planned to undergo a transplant during the time of the MedRec.New patient initiating maintenance hemodialysis.

### Who Will Take Informed Consent?

Not applicable (a waiver of consent was obtained for this quality improvement project; medication reviews are considered best practice in our institution for patients on dialysis).^
1
^

### Additional Consent Provisions for Collection and Use of Participant Data and Biological Specimens

No biological specimens will be collected as part of this trial.

### Interventions

#### Explanation of the choice of comparators

We are comparing the intervention on 2 of 3 outpatient hemodialysis units within the same hospital center. Although there are some differences between the patients on each unit, they are similar. The third unit is smaller and treats more medically complex patients, including those with active cancer and solid organ transplant. We selected our control and intervention units as they resemble typical community dialysis units to increase the external validity of our findings.

#### Intervention description

This study will build on existing policies aimed at optimizing medication therapy in patients undergoing maintenance hemodialysis. The electronic deprescribing decision support tool, MedSafer, now includes dialysis-specific deprescribing indications. For example, if a dialysis patient is receiving aspirin for primary prevention, MedSafer will generate a dialysis-specific deprescribing opportunity for the clinician stating the following: “The use of aspirin in dialysis patients increases the risk of bleeding. Also, there is little benefit of using aspirin in dialysis patients for primary prevention.” Patients who are receiving aspirin for secondary prevention will have this rule suppressed. In this way, deprescribing reports are individualized. The aspirin deprescribing opportunity is an example of a high-risk alert; a flag where the harms outweigh the benefits in most patients. Other categories include intermediate risk (harms and benefits need to be balanced and assessed by the clinician) and medications of little added value (no demonstrated value or evidence of no effect). Where relevant, tapering schedules are provided if the drug must be gradually discontinued and opportunities are linked to patient deprescribing empowerment brochures from the Canadian Medication Appropriateness and Deprescribing Network.^27,28^

The use of MedSafer reports during MedRecs will be tested in the dialysis setting, where nephrologists are regularly in contact with patients. MedRecs are an interdisciplinary clinical activity performed biannually on the hemodialysis units (in the Spring and Fall), and within 1 week following discharge from any hospitalization that occurs. This study will take place in the Fall of 2022.

The usual MedRec process occurs as follows: a dialysis nurse first validates with the patient their list of usual home medications and correlates this with the medication list provided by the pharmacy. Discrepancies between the patient’s medication list and the pharmacy’s medication list are resolved through discussion with the patient and pharmacy. Afterward, the treating nephrologist and the nurse review the patient’s list of medications and perform any necessary adjustments. The process is meant to avoid medication duplication, ensure appropriate dosing in the dialysis context, and avoid omissions. Deprescribing does not routinely take place as part of the MedRec process despite this being an opportune time to re-evaluate the ongoing necessity, harms, and benefits of PIMs. Currently, whether deprescribing occurs is nephrologist dependent.

Next, for the purpose of the study, the study lead ([name]) will enter the best medication history (described above), medications, and select laboratory values (hemoglobin A1c and serum creatinine) into MedSafer and generate reports for all patients in the study. The intervention unit (Lachine Hospital) will perform one of their usual biannual MedRecs paired with MedSafer deprescribing reports, including dialysis-specific deprescribing opportunities (the intervention). Reports will be pre-generated and provided to the interdisciplinary team, along with patient deprescribing empowerment brochures.

One of the deprescribing brochures will be a fact sheet on the topic of deprescribing, and others are given for select classes of medications (sedative-hypnotic drugs,^
29
^ gabapentinoids,^
30
^ proton-pump inhibitors [PPIs],^
31
^ and opioids for chronic non-cancer pain^
32
^). The control hemodialysis unit (Montreal General Hospital) will, concurrently, perform their usual biannual MedRec, in the absence of deprescribing reports or patient empowerment brochures.

MedSafer contains deprescribing opportunities from several existing guidelines for safer prescribing in older adults.^18,19,33^ As previously mentioned, the reports will be printed and placed in a study binder at the physician’s desk on the intervention unit and organized alphabetically according to the first letter of the last name of each patient. If MedSafer does not emit any recommendations, a report stating “no deprescribing opportunities were identified at this time” will be generated and placed in the binder.

Physicians on the intervention unit will receive a university-affiliated email from the study lead 2 weeks before the first planned start of the study to explain the workflow of the MedSafer MedRec process. They will be provided with a checklist to follow while they are performing MedRecs with the MedSafer reports as a guide. Study contact information is also provided for any support with the project. This guide (Supplemental Appendix) will ensure standardization of the MedRec process on the intervention unit. This initial email will also contain an example of a MedSafer deprescribing report. The treating physicians on the intervention unit will meet the study lead at the intervention site in person the day before the planned start of the study to review the MedSafer MedRec workflow and introduce them to the MedSafer reports and deprescribing brochures.

The patient deprescribing empowerment brochures (available in French and English) will be made available to the physician in the study binder, paired with the deprescribing reports. At the physician’s discretion, these will be provided to the patient to increase the motivation to deprescribe and provide an active learning opportunity for patients regarding their pharmacotherapy. Each patient on the intervention unit will receive a deprescribing fact sheet available in a third-grade-level language (Supplemental Appendix).

Ultimately, the decision of whether to deprescribe is left to the clinical reasoning of the treating team, and shared decision making with the patient will be encouraged, as this is a pragmatic intervention to study the real-world efficacy of making the deprescribing reports and brochures available in hemodialysis units.

#### Criteria for discontinuing or modifying allocated interventions

There are no planned interim analyses, as this is a quality improvement intervention that is considered best practice. Medication reconciliation for patients receiving maintenance hemodialysis occurs as part of usual care.

#### Strategies to improve adherence to interventions

Efforts will be made in this study to facilitate the ease of access to MedSafer reports and to iteratively improve the MedRec workflow through weekly “plan, do, study, act” cycles. To begin with, an introductory email will be sent to the nephrologists attending on the intervention unit. This email will contain an overview of the study, how it integrates with the existing workflow, and the expectations for the treating nephrologist (to review the MedSafer report at the time of performing a MedRec, perform any relevant deprescribing, provide the deprescribing brochures to the patient, and make a note in the electronic when the MedRec is complete). The study lead will generate sample MedSafer reports for the clinical team, so they can familiarize themselves with the report format prior to the intervention commencing. A physician nephrologist champion ([name]) will be available to answer any questions or concerns.

### Relevant Concomitant Care Permitted or Prohibited During the Trial

All usual care will be permitted, and no specific care is prohibited during the study.

### Provisions for Post-trial Care

Patients in the study will continue to receive usual (usually thrice weekly) care in the hemodialysis unit, post-intervention.

### Outcomes

The *primary outcome* will be the efficacy of MedSafer for deprescribing, based on the proportion of patients with 1 or more PIMs deprescribed, compared between the intervention and control units. This will be conditioned on patients with 1 or more PIMs at baseline. Deprescribing will be defined as any PIM that is identified by the MedSafer deprescribing algorithms, that is: stopped or deliberately reduced or tapered.

The key *secondary outcomes* will be the reduction in the mean number of prescribed drugs from baseline following a MedRec compared between the intervention and control units, and implementation barriers and facilitators collected from qualitative, semi-structured interviews with nephrologists on the intervention unit. The number of gastrointestinal bleeds will be reported in total and by intervention status.

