## Data Collection and Management

### Plans for Assessment and Collection of Outcomes

Baseline demographic data, the best possible medication history data, the most recent glycated hemoglobin as a measure of diabetes control, and creatinine will be collected for both the control and intervention unit from the electronic medical record (EMR), called NephroCare. These data will be input in the MedSafer web-based portal, and deprescribing reports will be generated for patients on the intervention unit.

Following a MedRec, medication changes will be captured from NephroCare and input into the MedSafer software for both the intervention and control units, permitting an analysis comparing deprescribing that took place on the 2 units.

At the time of MedRec, nephrologists will review the medication list of the patient (obtained from the EMR), validate the list with the patient, and then deprescribe when deemed appropriate (based on the MedSafer report). Medication changes will be faxed the same day to patient’s pharmacy. During this process, if a patient advises the clinical team that they are no longer taking a prescribed drug, this medication will be removed from the patient’s medication list in the EMR. If it is discovered that a patient has already discontinued a drug at the time of performing a MedRec, this will not be counted in the primary outcome of deprescribing.

At the end of the intervention, nephrologists who participated in MedRecs will be invited to participate in semi-structured interviews with the study lead to address their perceived facilitators and barriers related to deprescribing on the dialysis unit. Afterward, themes will be developed from the data collection, according to the grounded theory in qualitative research.^
34
^

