### Data Management

Manual baseline data entry for all patients will occur in the MedSafer web-based portal with data extracted from the NephroCare EMR by a trained study investigator. Any medication changes that occur are input into NephroCare at the time of performing the MedRec. When a MedRec occurs, the date is noted in the unit “task binder” located on site and accessible to all clinicians. MedRecs are considered up to date if they have been completed in the past 6 months and are only redone in the event a patient is hospitalized.

Before and after the MedRecs have been completed, each patient’s medication and comorbidity data will be updated in MedSafer, and a pre- and post-intervention medication dataset (coded by study ID) will be extracted and stored on a secure server. Analysis will be conducted on these coded datasets to record medication changes and deprescribing.

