## Discussion

This quality improvement study integrates electronic deprescribing decision support with the usual process of MedRec taking place on our dialysis units. To our knowledge, this is the first study to test the implementation of the new dialysis-specific deprescribing algorithms in a real-world setting. Potential implications of this quality improvement study include reducing the number of PIMs prescribed and decreasing pill burden by reducing the mean number of medications prescribed. This is a pragmatic study as it is built into the existing workflow for performing MedRec at our hospital center. As many dialysis units have similar MedRec procedures, we expect our findings would be scalable to other centers.

There are barriers to deprescribing during routine MedRec in hemodialysis. In fact, clinicians can lack sufficient time to complete a medication review and subsequently deprescribe; patient values and previous lived experiences with their medications, their perceived therapeutic effects, and potential adverse events are important factors to consider.^
37
^ Because of their chronic renal disease and complex medication regimens, patients on dialysis can also experience cognitive impairment that may affect the clinician’s ability to comprehensively perform medication reconciliation given already limited time constraints.^
21
^ Patients may also lack sufficient resources to learn about the medications they are taking, including their potential harms. The therapeutic relationship between the patient and the clinician can also influence initiation of a deprescribing trial or affect readiness to attempt a drug deprescription.^38,39^ This study aims to overcome these barriers through its methodology; we aim to address the lack of time by providing nephrologists with prepared deprescribing reports.

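### A flagged drug swapped at the same MedRec for another flagged drug of its class scores as a primary-outcome success

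*Protocol article*

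**What the plan says.** The Outcomes section defines the event drug by drug: "Deprescribing will be defined as any PIM that is identified by the MedSafer deprescribing algorithms, that is: stopped or deliberately reduced or tapered". The endpoint is then binary per patient, "based on the proportion of patients with 1 or more PIMs deprescribed, compared between the intervention and control units", among patients with at least one PIM at baseline.

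One event is ruled out. Under Plans for Assessment and Collection of Outcomes, if the MedRec reveals that the patient had already stopped a drug, "this will not be counted in the primary outcome of deprescribing". Nothing is said about a drug started at the same MedRec.

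The key quantitative secondary outcome is "the reduction in the mean number of prescribed drugs from baseline following a MedRec compared between the intervention and control units". It covers all drugs, not PIMs. Under Data Management, "a pre- and post-intervention medication dataset (coded by study ID) will be extracted and stored on a secure server", and this is done for both units.

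**The concern.** The event looks at one side of the medication change only. If a flagged drug leaves the list and another flagged drug of the same class enters it at the same MedRec, the definition is met, while the patient has as many PIMs and as many drugs as before. That sits badly with what the Discussion hopes for: "Potential implications of this quality improvement study include reducing the number of PIMs prescribed and decreasing pill burden by reducing the mean number of medications".

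Two things could follow. If swaps are equally common on both units, they raise both event rates, shrink the difference and cost power. If they are more common on the intervention unit, they produce a difference that reflects no fall in PIMs. The second case cannot be dismissed: physicians know which unit they work on, and only those on the intervention unit receive reports that name specific drugs. Replacing a named drug is one possible response to such a report, and the Discussion notes that patients may resist stopping for fear of rebound symptoms.

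**Working it through.** **Literal reading.** Three cases, each for a patient with one flagged PIM at baseline:

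| Change at the MedRec | Primary event | Change in PIM count | Change in drug count |
|---|---|---|---|
| Stopped, nothing started | yes | −1 | −1 |
| Dose deliberately reduced | yes | 0 | 0 |
| Stopped, another flagged PIM of the same class started | yes | 0 | 0 |

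The second row is included on purpose by the definition. The third is included only because nothing excludes it.

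**Inputs (Sample Size section).** 85 and 153 patients, about 90% with a PIM, control rate 10%, increase 15 points, two-sided alpha 0.05, power 80%. Analysed numbers: 0.9 × 85 = 76.5 and 0.9 × 153 = 137.7, taken as 76 and 138 (total 214, as stated).

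**The plan's own figure.** Two-proportion z-test, pooled variance under the null and unpooled under the alternative:

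power = Φ[(d − 1.96·SE0)/SE1], with d = pI − pC

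- Pooled rate = (76 × 0.25 + 138 × 0.10)/214 = 0.153.
- SE0 = √[0.153 × 0.847 × (1/76 + 1/138)] = 0.0515.
- SE1 = √[0.25 × 0.75/76 + 0.10 × 0.90/138] = 0.0559.
- Power = Φ[(0.15 − 0.1009)/0.0559] = Φ(0.88) = 81%.

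The stated 15-point detectable increase is reproduced. At 76 and 138 patients, 80% power is reached at 14.8 points, so there is almost no margin.

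**Adding swaps (assumed, since the article gives no rate).** Let a share s of patients have a same-class swap, independent of true deprescribing. The observed rate is 1 − (1 − p)(1 − s).

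Equal s on both units, true rates 10% and 25%:

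| s | Control | Intervention | Difference (points) | Power |
|---|---|---|---|---|
| 0 | 10.0% | 25.0% | 15.0 | 81% |
| 2% | 11.8% | 26.5% | 14.7 | 77% |
| 5% | 14.5% | 28.75% | 14.25 | 70% |
| 10% | 19.0% | 32.5% | 13.5 | 60% |

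Unequal s, no true effect (10% on both units):

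| s intervention / control | Observed rates | False difference (points) | Chance of p<0.05 favouring the intervention |
|---|---|---|---|
| 8% / 2% | 17.2% vs 11.8% | 5.4 | about 20% |
| 10% / 2% | 19.0% vs 11.8% | 7.2 | about 31% |

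For the last row, SE0 = 0.0501 and SE1 = 0.0527, so Φ[(0.072 − 0.0982)/0.0527] = Φ(−0.50) = 31%. The nominal rate in that direction is 2.5%.

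**The case against.** **The size is assumed throughout.** This stands. No section gives a swap rate, and a share of 10% would equal the whole planned control rate. The calculation also adds swaps on top of 10% and 25%, although the article does not say that those planning rates exclude them. The intervention materials may discourage same-class swaps: the brochures address whole classes, and the reports carry tapering schedules where relevant.

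**The secondary outcome is a safeguard.** In part. A one-for-one swap adds nothing to the reduction in mean number of drugs, so a primary result driven by swaps would lack support there. But that outcome counts every drug, cannot isolate PIM changes, and leaves the primary event as it is.

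**Scoring details belong in an analysis plan.** A fair point if the article were silent. It is not: it states a definition and one exclusion, and a swap meets that definition as written. If an unpublished plan already nets out swaps, the Outcomes text should say so.

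**Three stronger readings are tempting and not supported.**

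- A reader might infer that removing a duplicate entry also scores. If the drug continues under another entry, it has not been stopped. The Intervention description does say of the usual MedRec that "The process is meant to avoid medication duplication, ensure appropriate dosing in the dialysis context, and avoid omissions", but it also says that "Discrepancies between the patient’s medication list and the pharmacy’s medication list are resolved through discussion with the patient and pharmacy", and the medication history obtained this way is what goes into MedSafer. If the two entries are different drugs of one class, stopping one does lower the burden.
- A reader might infer that only a fall in PIM count is deprescribing. The definition expressly includes dose reduction and tapering, which leave the count unchanged.
- A reader might take fewer PIMs to be the stated goal. The Discussion lists it as a potential implication; the stated aim is to increase deprescribing.

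**Conclusion.** The gap is in the text and is certain: a same-class PIM-for-PIM replacement at the MedRec counts as deprescribing, and no listed outcome would show that the number of PIMs had not changed. Its effect is unknown. It runs from negligible, if swaps are rare, to a power of about 60% (10% of patients on both units), or a false difference of about half the 15-point target (7.2 points at 10% versus 2%). These figures rest on assumed swap shares, independence from true deprescribing, and a simple z-test in place of the planned mixed-effects model. They do not show that the result will be biased, and the documents give no evidence that swaps will differ between units. The point merits a change because the comparison is unblinded, only one unit receives drug-specific flags, the design has little spare power and the correction is cheap.

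**What to change.** Add to the Outcomes definition:

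- A stopped PIM does not count if another MedSafer-identified PIM of the same class is newly started at that MedRec, meaning absent from the pre-MedRec list and present on the post-MedRec list.
- Removing a duplicate entry of a drug that continues is not a stop. This only makes explicit what the definition already implies.
- Dose reductions and tapers still count, as does stopping one of two different PIMs of the same class. A patient with any other qualifying PIM remains a success.

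Fix the list of classes before outcome data are examined, apply the rule by program to the pre- and post-MedRec datasets of both units, and report the present definition as a sensitivity analysis.

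The rule should stay this narrow. Requiring that no same-class drug remains at an equal or higher dose would miss genuine stops and would need dose equivalence across drugs. Matching on indication would need data that the article does not list as collected.

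The cost is a few sentences, a class-level match in the code and a slightly lower event count. No new data are needed. This is a scoring rule and says nothing about what clinicians should prescribe.
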